## Methods

### Study Design

A pilot RCT is currently underway at 8 adult ICUs across Canada in collaboration with the Canadian Critical Care Trials Group. Ethics approval for the study was obtained from the Research Ethics Board (REB) at St Michael's hospital and the REBs of participating centres. Figure 1 provides an overview of the study.

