#### Study Randomization

Patients undergo stratified randomization within centres based on the presence (or absence) of (i) a diagnosis of known or suspected COPD [31,32] or (ii) a central neurologic disorder, provided that a study ventilator is available. In the event that both diagnoses are present, we prioritize central neurologic disorders during stratification.

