#### Statistical Analyses

Descriptive statistics including means, standard deviations, medians, interquartile ranges and frequency distributions will be used to summarize the data. For univariate analyses, we will use the Chi-square test (alternatively, Fisher's exact test when the expected value is ≤ 5) and Student's t-test (alternatively, the Mann-Whitney U-test, if normality assumptions are not satisfied) for binary and continuous outcomes, respectively. We will evaluate the percentage of (i) hours off-protocol and (ii) daily SAS scores < 2 or > 5 (or RASS equivalent) by treatment group. Compliance will be considered acceptable if ≥ 75% [that is; protocol violations (off protocol hours without meeting criteria to return to/remain on an alternate mode of mechanical ventilation) or SAS scores < 2 or > 5 (equivalent RASS -4 < or > +1) occur < 25% of the time]. SBT compliance will be considered acceptable if ≥ 75% of SBT opportunities are realized. We will compare average Likert scale scores based on clinician group and the weaning strategy utilized using Analysis of Variance (ANOVA). We will compare time to successful extubation and death between groups using time-to-event analysis with censoring of deaths and application of the log-rank test. We will consider p-values ≤ 0.05 to be statistically significant.

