#### Sample Size

Estimates are not available to allow precise sample size estimation of the primary outcome for the multicentre pilot RCT. To ensure that the study protocols are easy to follow before engaging in a definitive weaning RCT, we estimate that a total of 90 patients (ideally approximately 11-12 patients per site) are required to assess protocol compliance. To ensure that all centres gain some experience with both protocols, we set a maximum site enrolment of 35 patients.	

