## Conclusion

The WEAN pilot study was designed to evaluate clinician compliance with and acceptance of the proposed weaning and sedation protocols. In addition, we will ascertain whether centres can recruit the desired patient population. Strengths of the WEAN Study include the use of central randomization, allocation concealment, stratification (to ensure equal distribution of conditions that may prolong ventilation) and the use of protocols in both arms to limit treatment and performance bias. To this end, both treatment arms use pressure support and include opportunities to undergo SBTs. Moreover, they share a common PEEP/FiO_2 _chart, sedation protocol, extubation and reintubation criteria, and criteria for NIV use for post-extubation respiratory failure. The major threat to the validity of the pilot RCT is that it is, out of necessity, unblinded. To this end, we developed detailed weaning and sedation protocols to limit potential sources of bias and standardize weaning and sedation administration in both study arms and across participating centres. While we can not blind clinicians, patients and data collectors, we will blind the data analyst to treatment group assignment until the planned statistical analyses are completed. As the first multicentre weaning RCT in Canada, the WEAN Study seeks not only to determine the feasibility of conducting a large scale future weaning trial, but to establish a collaborative network of ICU clinicians dedicated to advancing the science of weaning.

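### Randomization is stratified by diagnosis within centres, but the between-arm tests named, chiefly the log-rank for time to successful extubation, ignore the strata and may lose power

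*Protocol article*

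**What the plan says.** **Design.** Protocol article, Study Randomization: "Patients undergo stratified randomization within centres based on the presence (or absence) of" COPD or a central neurologic disorder. For patients with both, "In the event that both diagnoses are present, we prioritize central neurologic disorders during stratification". Diagnosis therefore has three levels: neurologic, COPD, neither. Study Design gives the number of centres: "A pilot RCT is currently underway at 8 adult ICUs across Canada". The Conclusion lists this feature among the strengths: "stratification (to ensure equal distribution of conditions that may prolong ventilation".

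**Analysis.** Statistical Analyses names chi-square or Fisher's exact test for binary outcomes and Student's t-test or Mann-Whitney for continuous ones. It names ANOVA by clinician group and weaning strategy for acceptance scores. For time to successful extubation and death it names a time-to-event comparison with "application of the log-rank test". The significance rule is "We will consider p-values ≤ 0.05 to be statistically significant". None of these tests is said to carry diagnosis or centre.

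**Size.** The Sample Size section states that "a total of 90 patients (ideally approximately 11-12 patients per site) are required to assess protocol compliance", and that "Estimates are not available to allow precise sample size estimation of the primary outcome for the multicentre pilot RCT". No power, effect size or event rate is claimed.

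**The concern.** Stratified randomization balances the arms on the stratum factors. If those factors predict outcome, the between-stratum variation no longer contributes to chance differences between arms. An unadjusted test still counts it in its standard error. The test then rejects less often than its nominal level under the null and detects a true effect less often. The plan goes to the trouble of stratifying but does not collect the gain in precision.

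What is at stake is power in the secondary between-arm comparisons of ventilation and stay, which are formal tests at the 0.05 level in only 90 patients.

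**Working it through.** **Inputs from the article.** 90 patients, 8 centres, 3 diagnostic levels, significance at 0.05 (two-sided assumed).

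- Patients per centre: 90 ÷ 8 = 11.25, which agrees with the article's 11-12 per site. This is its only sample-size arithmetic; there is no power figure to reproduce.
- Randomization cells: 8 x 3 = 24. Patients per cell: 90 ÷ 24 = 3.75.

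**Inputs assumed, because the article gives none.** Diagnosis mix, stratum effects, treatment effect, 1:1 allocation and permuted blocks of 4.

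**Step 1: analytic size for a continuous outcome.** Let R² be the share of outcome variance explained by the strata. Adjusted over unadjusted standard error = √(1 − R²). With 45 per arm and a standardized difference of 0.6 (assumed), the unadjusted standard error is √(2/45) = 0.211. Then 0.6 ÷ 0.211 = 2.85, and power = Φ(2.85 − 1.96) = 81%. After adjustment, power = Φ(2.85 ÷ √(1 − R²) − 1.96).

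| R² | SE ratio | Power, adjusted |
|---|---|---|
| 0 | 1.00 | 81% |
| 0.05 | 0.975 | 83% |
| 0.10 | 0.95 | 85% |
| 0.20 | 0.89 | 89% |
| 0.30 | 0.84 | 93% |

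**Step 2: time to event, diagnosis effects only.** Assumptions: diagnosis mix 50% neither, 25% COPD and 25% neurologic; true extubation hazard ratio 1.8; and 4,000 trials per scenario.

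| Hazard ratios, COPD and neurologic vs neither | Plain log-rank | Stratified by diagnosis | Gain (points) |
|---|---|---|---|
| 0.7 and 0.7 | 69.1% | 68.6% | −0.5 |
| 0.5 and 0.4 | 57.6% | 62.6% | 5.0 |
| 0.4 and 0.3 | 50.7% | 60.3% | 9.6 |

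**Step 3: time to event, diagnosis and centre effects together.** Assumptions: diagnosis mix 60% neither, 20% COPD and 20% neurologic; treatment hazard ratio 2; centre SD s and diagnosis effect d on the log-hazard scale. R² = v / (1 + v), with v = s² + 0.24 d² (0.24 = 0.4 x 0.6). For s = 0.4 and d = 0.6, v is the sum of 0.16 and 0.086, which is 0.246, and R² = 0.20. Log-rank columns use 3,000 trials; the Cox column uses 600, with the plain log-rank in those same 600 trials in brackets.

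| R² | Plain log-rank | Stratified by diagnosis | Stratified on 24 cells | Cox adjusted for diagnosis |
|---|---|---|---|---|
| 0 | 84% | 82% | 67% | 84% (84%) |
| 0.06 | 82% | 81% | 65% | 82% (82%) |
| 0.20 | 73% | 74% | 64% | 79% (74%) |
| 0.34 | 65% | 69% | 63% | 69% (63%) |

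The gain from a diagnosis-stratified log-rank is smaller here (about 1 and 4 points at the two higher R² values), because part of R² belongs to centre. Stratifying on 24 cells is worse than the plain test in every row.

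**Step 4: continuous outcome, same scenarios.** Power of the t-test against ANCOVA on centre and diagnosis:

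| Test | R² 0 | R² 0.06 | R² 0.20 | R² 0.34 |
|---|---|---|---|---|
| T-test | 80% | 79% | 73% | 67% |
| ANCOVA | 79% | 79% | 80% | 80% |

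These gains use both factors, so they are an upper guide to what diagnosis alone would recover.

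**Step 5: type I error at a nominal 5%.**

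| Test | R² 0 | R² 0.06 | R² 0.20 | R² 0.34 |
|---|---|---|---|---|
| Plain log-rank | 5.7% | 5.7% | 3.9% | 3.0% |
| T-test | 5.7% | 4.5% | 3.7% | 2.4% |
| ANCOVA | 5.8% | 5.1% | 4.8% | 4.4% |
| Cox with fixed centre effects | 8.2% | 7.2% | 8.5% | 7.2% |

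The Monte Carlo standard error is √(0.05 x 0.95 ÷ 3,000) = 0.4% for the first three rows and √(0.05 x 0.95 ÷ 600) = 0.9% for the last. The 5.7% values are therefore compatible with 5%. The conservatism at the two higher R² values, and the excess with fixed centre effects, are larger than simulation noise.

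**The case against.** The strongest reply is that this is a feasibility pilot. Its primary outcome is compliance, judged against a fixed 75% threshold, and the 90 patients were chosen for that purpose. A plain log-rank is a valid test whose error here is on the safe side. The chi-square and t-tests are labelled univariate, and a fuller analysis plan may add adjusted models. Most of this stands, and it limits the point to precision in secondary comparisons. It does not remove the point: the log-rank is named as the planned comparison for time to extubation, and it omits factors that the article itself gives as its reason for stratifying.

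A reader might infer more than the article supports:

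- **That the strata are prognostic, so true type I error is below 5%.** The article says only that the conditions may prolong ventilation and gives no effect size. With weak strata there is neither conservatism nor power loss.
- **That 90 patients are too few.** No power was claimed, so no stated figure is wrong.
- **That a biased hazard ratio will be reported.** No hazard ratio is planned. A marginal and a diagnosis-conditional hazard ratio are in any case different quantities, and neither is an error.
- **That a definitive trial will be sized from these estimates.** The article speaks of compliance, acceptance, recruitment and feasibility, and nowhere says this.

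A fair objection also applies to broad remedies. Mantel-Haenszel or covariate models for every outcome would not suit the sparse binary and skewed outcomes for which the plan keeps Fisher's exact and Mann-Whitney tests.

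**Conclusion.** The point holds as a free improvement in precision. The design stratifies by diagnosis within centre, and the between-arm tests named, chiefly the log-rank for time to successful extubation, ignore those strata. If the strata are prognostic, the tests are conservative and lose power. For time to extubation the loss is about 0 points with weak strata and roughly 5 to 10 with moderate to strong strata. A diagnosis-stratified log-rank recovers less than that where much of the stratum effect lies between centres. These sizes rest wholly on assumed stratum effects, diagnosis mix, block size and treatment effect. Validity, the primary compliance criterion and the sample size of 90 are untouched.

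**What to change.** In Statistical Analyses:

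1. Replace the plain log-rank for time to successful extubation with a log-rank stratified by the three diagnostic groups used at randomization, or a Cox model adjusted for diagnosis. Choose one in advance. In the checks above, the Cox model kept the plain test's power when strata were weak and gained more than the stratified log-rank at R² 0.20.
2. For continuous duration outcomes, add diagnosis as a covariate where model assumptions hold, after transformation if needed. Otherwise use a rank test stratified by diagnosis.
3. Keep Fisher's exact test for sparse binary outcomes.
4. State that the time-to-event analysis will not be stratified on all 24 centre-by-diagnosis cells and will not use fixed centre effects in a Cox model.

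The cost is wording only. Diagnosis is recorded at randomization, so no data, visits or patients are added. The change should be made before the data analyst, whom the article keeps blinded until the planned analyses are complete, learns the treatment assignment.

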### Objectives

The primary objective of the multicentre pilot study comparing SmartCare™ [hereafter referred to as "Automated Weaning"] and "Protocolized Weaning" is to evaluate compliance with the weaning and sedation protocols among intubated patients requiring > 24 hrs of invasive ventilation.

The secondary objectives of the multicentre pilot RCT are to evaluate clinician acceptance of the alternative weaning and sedation protocols using a Visual Analogue Scale daily, and to demonstrate the ability to recruit the desired patient population. In this manner, we will assess the feasibility of conducting a future, definitive weaning RCT in Canada.

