#### Study Outcomes

The primary outcome of the WEAN pilot study is compliance with the weaning and sedation protocols. Secondary outcomes include (i) daytime clinician (nurse; RRT and physician) acceptance of the sedation and weaning protocols, respectively, (ii) time to successful extubation defined as the time from randomization to unsupported (no requirement for NIV or invasive ventilation), spontaneous breathing for ≥ 48 hours after extubation (or disconnection with a tracheostomy), (iii) time to completion of a successful SBT, (iv) total duration of mechanical ventilation (time from intubation to termination of ventilation), (vi) ICU and hospital length of stay, (vii) ICU and hospital mortality, and the proportion of patients (viii) developing nosocomial pneumonia [39], (ix) with weaning (self-extubation, tracheostomy, reintubation and prolonged mechanical ventilation >21 days) or ICU (myocardial infarction and pneumothoraces) complications, and (x) requiring NIV. Any NIV use is considered clinically relevant.

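### An unrestricted p ≤ 0.05 significance rule covers roughly 11 to 19 secondary comparisons in a feasibility pilot sized only for compliance

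*Protocol article*

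**What the plan says.** Study Outcomes defines the main question as one of feasibility: "The primary outcome of the WEAN pilot study is compliance with the weaning and sedation protocols". It then lists clinician acceptance and a series of clinical outcomes as secondary: times to successful extubation and to a successful SBT, duration of ventilation, lengths of stay, mortality, pneumonia, weaning and ICU complications, and use of NIV.

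Statistical Analyses gives a general test rule for binary and continuous outcomes, "Chi-square test (alternatively, Fisher's exact test when the expected value is ≤ 5) and Student's t-test" with a Mann-Whitney alternative. It adds ANOVA for the acceptance scores and a log-rank test for the time-to-event outcomes. Compliance is judged acceptable at 75% or more. The paragraph ends: "We will consider p-values ≤ 0.05 to be statistically significant".

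Sample Size states "Estimates are not available to allow precise sample size estimation of the primary outcome for the multicentre pilot RCT", and then "we estimate that a total of 90 patients (ideally approximately 11-12 patients per site) are required to assess protocol compliance". Objectives sums up the purpose: "In this manner, we will assess the feasibility of conducting a future, definitive weaning RCT in Canada".

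**The concern.** The significance rule and the purpose of the trial pull in different directions. The primary outcome does not use a p-value, so the rule serves mainly the comparisons that the pilot was not sized to make. The Discussion leaves the effect of the two strategies on important clinical outcomes to a later full-scale trial.

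Followed literally, the rule lets any one of many secondary comparisons be called statistically significant. The article's Conclusion names the lack of blinding as the major threat to validity, and its Background describes two earlier randomized trials with conflicting results. In that setting a chance finding could be read as evidence of benefit or harm and could complicate the definitive trial. Planning that trial calls for effect estimates with their uncertainty, which a significance label does not supply.

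**Working it through.** **The plan's own figure.** The 90 patients cannot be reproduced: the article gives no effect size, rate, standard deviation, alpha or power, and says that estimates are unavailable. There is thus no sizing for any clinical outcome to check.

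**Counting the comparisons (Study Outcomes).** The article does not name a test for each outcome, so the count follows from its general test rule.

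- Time to successful extubation 1, time to successful SBT 1, duration of ventilation 1, length of stay 2 (ICU, hospital), mortality 2 (ICU, hospital), pneumonia 1, NIV 1: subtotal 9.
- Complications: 2 if weaning and ICU complications are each one proportion, or 6 if each listed event is tested (4 weaning, 2 ICU).
- Clinical total: 9 + 2 = 11, or 9 + 6 = 15.
- Up to 3 acceptance comparisons, and 1 more if time to death has its own log-rank test: 15 + 3 + 1 = 19.

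**Chance of at least one p ≤ 0.05 with no true difference.** Two-sided tests are assumed, since the article does not state sidedness.

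Under independence the chance is 1 − 0.95^k:

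- k = 11: 1 − 0.95^11 = 0.431
- k = 15: 1 − 0.95^15 = 0.537
- k = 19: 1 − 0.95^19 = 0.623

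The 50% mark is passed only from k = 14 (0.512; k = 13 gives 0.487). The expected number of false positives is 0.05k: 0.55, 0.75 and 0.95.

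For equally correlated normal test statistics with correlation ρ (an assumption), the chance is 1 − ∫ [Φ((1.96 − √ρ·c)/√(1−ρ)) − Φ((−1.96 − √ρ·c)/√(1−ρ))]^k φ(c) dc:

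| k | independent | ρ = 0.3 | ρ = 0.5 |
|---|---|---|---|
| 11 | 43% | 37% | 30% |
| 15 | 54% | 46% | 36% |
| 19 | 62% | 53% | 41% |

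**Rare binary outcomes.** At 45 per arm (equal allocation assumed), exact enumeration of the planned Chi-square/Fisher rule gives an actual size of about 0.006 at a 5% event rate, 0.024 at 10%, 0.046 at 15% and 0.053 at 20%. The article gives no event rates. Three assumed sets for the ten binary outcomes, spanning 2% to 30%, give an independent-test chance of 39% to 51% for k = 15 and 50% to 60% for k = 19. Correlation would lower these further; the two effects were not combined.

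**The case against.** The best defence is that this is a generic convention sentence in a condensed article. Confidence intervals, exploratory labels and multiplicity handling are commonly left to a full protocol or SAP, so their absence here is no fault. That is accepted, and the point does not rest on it. It rests on a rule the article does state, without limit, and which does not fit the purpose it also states.

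The defence can add that the article frames itself as a feasibility study throughout and nowhere plans an efficacy claim. That also stands. A reader might infer that the authors intend to claim clinical benefit, but the documents do not say so. They only leave the wording open to it.

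A reader might also infer that a chance positive result is more likely than not. The documents do not support this as a general statement. It needs at least 14 tests and near-independence. The complications item can be read as two proportions, giving 11 clinical comparisons and 43% even under independence. The outcomes also plainly overlap: ventilation beyond 21 days is a cut of ventilation duration, time to extubation forms part of total duration, ICU deaths are among the hospital deaths, and length of stay tracks these. Finally, the calculation assumes no true difference on any outcome, which the conflicting earlier trials neither establish nor exclude.

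These objections reduce the size of the problem. They do not bring it near 5% in any scenario computed.

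**Conclusion.** The point holds at modest severity. The article applies an unrestricted p ≤ 0.05 rule to roughly 11 to 19 secondary comparisons in a pilot justified only by compliance. With no true differences, the chance of at least one 'significant' result is about 43% to 62% under independence, which should be read as an upper case, and about 30% to 53% at correlations of 0.3 to 0.5. Conservative Fisher tests on rare events would bring it lower. These figures depend on the count, on two-sided testing, on the assumed correlation and on no true difference anywhere.

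The compliance conclusion is not touched. Nor do the documents support reading this as a missing multiplicity correction: none is needed for a feasibility aim once the clinical comparisons are treated as exploratory.

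**What to change.** Replace the closing sentence of Statistical Analyses with:

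> Between-arm comparisons of secondary clinical outcomes are exploratory; they are reported as effect estimates with 95% confidence intervals, any p-values are descriptive, and no outcome will be used to claim efficacy.

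The cost is this wording plus confidence intervals in the results tables. Design, sample size, data collection and the 75% compliance criteria stay as they are. The downside is that the pilot gives up the option of declaring a significant clinical effect, a claim it was not sized to support. If a SAP exists, it should carry the same statement.

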#### Sample Size

Estimates are not available to allow precise sample size estimation of the primary outcome for the multicentre pilot RCT. To ensure that the study protocols are easy to follow before engaging in a definitive weaning RCT, we estimate that a total of 90 patients (ideally approximately 11-12 patients per site) are required to assess protocol compliance. To ensure that all centres gain some experience with both protocols, we set a maximum site enrolment of 35 patients.	

## Discussion

Life support technology interventions account for 5-10% of acute care bed occupancy and 34% of hospital budgets [41]. Current demands are expected to escalate in the future as the middle sector of our population ages [42]. Since up to 40% of the time on mechanical ventilation is related to weaning, Automated Weaning holds promise as a strategy to reduce ICU length of stay and the total time spent on mechanical ventilation by reducing weaning time, and weaning and ICU-related complications. More importantly, Automated Weaning may reduce the burden of illness related to protracted invasive ventilation and improve patient-important outcomes [43]. A key benefit of SmartCare™ is that weaning is unencumbered by limited clinician availability in the busy ICU setting. Prior to conducting a full scale RCT comparing the effect of the alternative weaning strategies on important clinical outcomes, we designed a feasibility RCT to assess clinician compliance with and acceptance of the detailed weaning and sedation protocols [44].

In the absence of evidence regarding the current 'standard of care in weaning' in Canada, we developed, tested and administered a questionnaire to RRT and physician leaders using rigorous survey methodology [45] to identify key aspects of weaning (use of protocols, daily screening, conduct of SBTs, preferred methods of support) at Canadian teaching hospitals. In this manner, we identified that daily screening and pressure support were common features of weaning and that most centres conduct SBTs using one of three strategies [46]. The results of the National Weaning Survey informed the design of the paper-based weaning protocol (control arm) in the WEAN Study.

Prior to initiating the multicentre WEAN Study, we conducted a run-in phase study involving two patients per centre. We randomized the first participant at each centre to either Automated or Protocolized Weaning and assigned the second patient to the alternate weaning strategy. We conducted the run in phase to ensure that participating centres could implement the detailed weaning and sedation protocols and complete the case report forms. Mechanical ventilation studies require detailed daily data collection and for protocols to be operationalized continuously. Following review of run in phase study procedures, a clinical evaluation committee approved sites to proceed with enrollment in the WEAN pilot RCT.

